## Method

### Participants

50 right-handed, healthy, native speakers of Indonesian will participate, and be tested at the Hong Kong Polytechnic University. All the participants will be tested using an Indonesian translation of the short form of the Edinburgh Handedness Inventory [34] to ensure that they are classified as right-handed. Participants will provide informed consent and will be financially compensated. As a power analysis is not possible due to the lack of previously studies on non-anomalous sentence processing, we will use a heuristic estimate of the sample size needed by doubling the largest sample size of previous relevant studies we found on non-anomalous sentence processing: Jackson, Lorimor, & van Hell [15] had 25 participants, and therefore the proposed study will recruit 50 participants. We will recruit participants from both within the university (students and/or staff) as well as outside of it. The participants will have to complete a language background questionnaire to ensure that they have first-language or equivalent proficiency in Indonesian. This study was approved by the Hong Kong Polytechnic University’s Institutional Review Board (ref no. HSEARS20211223003). Written consent will be obtained from participants.

### Materials

Participants will read stimuli comprising 100 semantically reversible active and passive sentences (see S1 Appendix in S1 File). Examples of which are shown in Table 2.

**Table 2 pone.0272207.t002:** Stimuli examples of each condition.

Condition	NP1	Art	VP	Adjunct	NP2	PP/RC
Active	Polisi	itu	menembak	langsung	seorang perampok	di malam hari.
	Police	that/the	**ACT**shoot	immediately	(a) robber	at night.
		(the/a) police immediately shoots (the/a) robber at night.				
Passive	Polisi	itu	ditembak	langsung	oleh perampok	di malam hari.
	Police	that/the	**PAS**shoot	immediately	by robber	at night
		(the/a) police is immediately shot by (the/a) robber at night				

The sentences involve an animate subject and object and are constructed while avoiding a plausibility bias. Word order is manipulated by using two structures: simple active and simple passive sentences. Based on previous studies on processing well-formed sentences, the contrast of interest is passive-active, and whether the effects of the word order persist. We will strive for active-passive pairing plausibility with the use of NP1 and NP2 that are plausibly reversible (i.e. each sentence should not be strongly biased to one interpretation due to the nouns used). Additionally, there will be 200 filler trials consisting of questions (e.g. What did the adventurer notice yesterday?) and cleft sentences (e.g. it is the boy who the girl is calling) to prevent the habituation of the participants. The task for both the experimental and filler sentences will be discussed in the Procedure. The stimuli will be tested for acceptability and prototypicality using an online survey method utilizing a Likert scale of 1 to 7 with a similar setup used by Jackson, Lorimor, & van Hell [15]. Assuming the materials are rated acceptable and plausible by raters, the materials will not be further edited.

The materials will be presented visually and word-by-word for 500ms with a 100ms blank screen between each word. Each trial begins with a blank screen of 750ms followed by the word ‘*siap*?’ (ready?), which stays on the screen until participants presses any keys. There will be two lists of sentences each pseudorandomized into 10 sets (each set containing 10 experimental sentences and 20 fillers). Digital triggers will be manually inserted at three time points in every sentence: at the onset of the verb (i.e., the onset of the prefix), and at the onset of NP2. Additionally, NP1 data points will be extracted from -1400 to -200 before the verb onset to be used as a sanity check to see if there are baseline differences between the conditions. It is important to note that the triggers will be located in the middle of the sentence.

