## Abstract

Previous studies of multiple languages have found processing differences between patient-first and agent-first word orders. However, the results are inconsistent as they do not identify a specific ERP component as a unique correlate of thematic role processing. Furthermore, these studies generally confound word order with frequency, as patient-first structures tend to be infrequent in the languages that have been investigated. There is evidence that frequency at the sentence level plays a significant role in language processing. To address this potential confounding variable, we will test a language where the non-canonical sentences are more frequent and are comparable to the canonical sentences, namely Standard Indonesian. In this language, there is evidence from acquisition, corpus, and clinical data indicates that the use of passive is frequent and salient. One instance of this difference can be demonstrated by the fact that it has been suggested that frequency may be the reason why Indonesian-speaking aphasic speakers do not have impairments in the comprehension of passives, whereas speakers of other languages with aphasia often do. In the present study, we will test 50 native speakers of Indonesian using 100 sentences (50 active and 50 passive sentences). If the neural correlates of thematic role processing are not observed in the critical region of the sentence (the prefix of the verb), this would suggest that the previous results were indeed influenced by frequency, but if we find that specific ERPs are connected to the hypothesized syntactic operations, this would further reinforce the existing evidence of the increased cognitive load required to process more syntactically complicated sentences.

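### In the design shown by Table 2 the passive reverses the event of its active partner, so event direction is aliased with voice, and neither the norming rule nor any stated use of the two lists removes a resulting plausibility difference

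*Protocol article*

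**What the plan says.** In Materials, Table 2 of the protocol article shows one pair. The active is glossed "the/a) police immediately shoots (the/a) robber at night" and the passive "the/a) police is immediately shot by (the/a) robber at night". The first noun phrase (NP1) is Polisi in both; only the verb prefix and the wording of the second noun phrase (NP2) change. The sample comprehension questions under Procedure name both events.

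The authors see the plausibility risk. Materials says that the nouns are animate and chosen to be reversible: "We will strive for active-passive pairing plausibility with the use of NP1 and NP2 that are plausibly reversible". Norming is planned: "The stimuli will be tested for acceptability and prototypicality using an online survey method utilizing a Likert scale of 1 to 7". The rule that follows is: "Assuming the materials are rated acceptable and plausible by raters, the materials will not be further edited".

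On lists, Materials says: "There will be two lists of sentences each pseudorandomized into 10 sets (each set containing 10 experimental sentences and 20 fillers". It does not say what differs between them. The Abstract gives the stimulus set: "we will test 50 native speakers of Indonesian using 100 sentences (50 active and 50 passive sentences".

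The Statistical analysis plan section compares active and passive ERPs by switching voice labels within participants. The test it describes has no item term and no rating term, and it covers the whole post-stimulus epoch.

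**The concern.** The study exists to remove one confound, structural frequency, from the passive-active contrast. If NP1 is kept and the verb changes voice, who does what to whom also reverses. A reader who finds police shooting a robber more (or less) expected than the opposite may respond to that rather than to role assignment.

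The norming rule is absolute: a sentence has to be good enough. It is not comparative. A set whose passives were all acceptable but on average somewhat less plausible than their actives would pass and be used.

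The consequence runs both ways. A plausibility difference could appear as a voice effect; the Introduction itself links the N400 to semantic incongruence and sentence-meaning integration. A difference of the opposite sign could hide a real voice effect, and Predictions reads a null result as evidence that earlier findings reflected frequency.

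**Working it through.** **1. List sizes (Materials, Procedure, Abstract).**
- Experimental sentences per list: 10 sets × 10 = 100.
- Trials per list: 10 × (10 + 20) = 300, which agrees with 10 blocks × 30 and with 100 experimental + 200 filler trials.
- Stated stimulus set: 50 active + 50 passive = 100.

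Each list is therefore as large as the whole stated set. On the Abstract's wording the two lists can differ only in order.

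**2. Aliasing within a pair.** Code voice as −1 (active) or +1 (passive). Code direction as −1 (noun A acts on B) or +1 (B acts on A).
- Table 2, with A always first: active (−1, −1), passive (+1, +1). The correlation is 1.0, and intercept, voice and direction have rank 2 of 3, so they are not separable.
- Rotating voice between lists while keeping A first gives the same two combinations, so the correlation stays 1.0.
- Mirroring noun roles between lists gives all four combinations: correlation 0, rank 3 of 3.

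**3. What enters the contrast.** Let v be the voice effect (passive minus active) and d the effect of direction (B acts on A, minus A acts on B), assumed additive.
- A first: passive − active = v + d.
- B first: passive − active = v − d.
- Mean of two equal lists: [(v + d) + (v − d)] / 2 = v.

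**4. Where it can act.** Each word takes 500 + 100 = 600 ms, and epochs end at 1000 ms.
- Verb epoch: in Table 2 an adjunct stands between verb and NP2, so NP2 starts 2 × 600 = 1200 ms after verb onset, outside the epoch. Only the fit of NP1 as agent or patient of that verb can act here.
- NP2 epoch: in Table 2, NP2 is two words (seorang or oleh, then the noun). If the trigger is on the first word, the noun appears at 600 ms, after the predicted 300–600 ms negativity but with 1000 − 600 = 400 ms of tested epoch left. If the trigger is on the noun, the predicted window overlaps with a response to the event.

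**5. Illustration on assumed inputs.** The article gives no effect size, SD or ratings. Take one window, a two-sided paired t-test at 0.05, 50 participants, no true voice effect, and an assumed SD of 1.5 to 3.0 µV for the participant-level difference. The noncentrality is bias / (SD/√50), with 49 degrees of freedom.

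| Assumed mean plausibility-driven difference | Rejections, SD 3.0 to SD 1.5 µV |
|---|---|
| 0 µV | 5% |
| 0.25 µV | 9% to 21% |
| 0.5 µV | 21% to 64% |
| 1.0 µV | 64% to 99.6% |

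For 0.5 µV the noncentrality is 0.5 / (3.0/7.07) = 1.18 to 0.5 / (1.5/7.07) = 2.36. The planned test is a cluster test, so these figures show only how such a bias would behave. They do not estimate this study.

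**The case against.** The strongest reply has four parts.

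- **One pair is shown.** A reader might infer that all 50 passives reverse their actives. Table 2 offers examples only; the full stimuli are in the S1 Appendix, which is not shown, and no sentence says that NP1 is constant throughout. This stands: beyond the pair shown, the reversal is an inference.
- **Aliased direction is not yet biased plausibility.** A reader might infer that plausibility is confounded with voice. That needs NP1 nouns to be, on average, better or worse agents than patients, and the article gives no evidence either way. With no direction effect nothing is inflated. The authors also plan reversible nouns and ratings. This stands, but those steps do not require the two voices to be matched.
- **Silence about the lists.** It is tempting to say that the lists are not used to cancel the effect. Their purpose is simply unstated, an article may leave list content to fuller materials, and Materials could mean 100 sentences per participant from a larger set. This stands in part. The arithmetic with the Abstract leaves no room for a role swap, and an ordinary rotation of voice would not help.
- **Weak mechanism in the main region.** The focus is mainly the verb, where the event is still incomplete and the prediction is a positivity at 500–700 ms. This stands: the two regions are not equally exposed, and overlap with the predicted NP2 negativity depends on trigger placement. The test nevertheless covers the whole epoch.

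Keeping NP1 fixed also has a real merit: the material before the verb is identical across voices. The change proposed below keeps that.

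**Conclusion.** The point holds in limited form. In the design that Table 2 shows, event direction is fully aliased with voice within a pair. The stated rule for keeping materials does not compare the voices, and the stated test cannot separate the two effects. A mean difference in how well first nouns fit the agent and patient roles would pass norming and enter the contrast in full.

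The size cannot be given from the article, and the sign is unknown. The conclusion assumes that the other pairs are built like the example and that the set is the 100 sentences named in the Abstract. The documents do not support saying that the passives are less plausible, or that an N400-like plausibility effect would coincide with the predicted NP2 window. This is an inexpensive improvement to make before data collection; it does not show that the study would give a wrong answer.

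**What to change.** State what differs between the two lists, and use them to mirror noun roles:

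- List 1: 'police shoot robber' and 'police are shot by robber'.
- List 2: 'robber shoots police' and 'robber is shot by police'.

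Split participants equally, 25 per list. NP1 then stays identical across voice within a list, so the verb baseline and the planned pre-verb check keep their meaning, and each event occurs in both voices across lists. Keep the lists balanced after exclusions: with n1 and n2 analysed, the fraction of a mean direction effect left in the pooled contrast is (n1 − n2)/(n1 + n2).

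In addition, compare the norming ratings of the active and passive members of each pair, and replace clearly mismatched pairs by a criterion fixed in advance. State also which word carries the NP2 trigger.

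Cost: if the set is 50 pairs, 50 × 2 = 100 further sentence versions to build and add to the online norming. Some items may not work in the swapped direction and would need replacing. No extra EEG time is needed.

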### Procedure

Participants will read the participant information sheet, fill out a questionnaire about their demographic details, and sign the informed consent form.

Participants will be seated in front of a presentation monitor on which the sentences will be presented using E-Prime software, and the experiment will start with written instructions that will be explained orally by the experimenter. During the whole experiment, a fixation cross will be shown between trials and sets. Prior to the experiment, participants will be instructed to minimize their head movements during the trials and not to close their eyes while performing the experiment, although they will not be asked to refrain from blinking.

After every 3–8 trials (randomized), participants will be given a comprehension prompt. For the experimental items and filler cleft sentences, the comprehension prompt will be a yes/no question to probe the thematic role assignment (e.g., Did the police shoot the robber?/Did the robber shoot the police?). For the filler questions, the comprehension prompt will be a sentence that appropriately responds to the question (e.g., the adventurer noticed an officer patrolling) or if the noun phrase in the question is presented as the theme (e.g., the officer called the adventurer), and participants will have to judge whether the sentence is an appropriate response to the question (e.g., they should respond "yes" if they see "the adventurer noticed an officer patrolling" after this filler). These prompts are designed to ensure that the participants remain focused and parse the trials displayed, as well as to provide a measure of comprehension performance.

To avoid fatigue, there will be pauses after every block consisting of 30 trials (10 blocks in total), where the participants can take a break and resume the experiment whenever they are ready. The total test session, including cap and electrode preparation, will take approximately one and a half hours per participant.

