### Data exclusion criteria

Participants may be excluded based on our predetermined data exclusion criteria, which include the following:

Minimum number of trials after artifact rejection: We determine a preset number of 25 trials per condition as a minimum. Any participant having fewer than 25 trials in any condition after artifact rejection will be excluded from the analysis.Missing information/data: If a participant refuses to complete all or part of the questionnaire about her/his demographic information or the handedness inventory, or if a technical issue leads to missing data/a subset of missing data for a participant, the individual will be excluded from the analysis.Bad channels (1): The threshold for data exclusion is at or over 15% of the electrodes (9 or more) being unusable due to excessive artifacts or environmental noise. This is in the event that these channels cannot be interpolated due to positioning (for example, multiple bad channels being adjacent to each other and therefore not having enough neighbouring electrodes for interpolation).Bad channels (2): A second criterion is if a number of bad channels cluster or are adjacent to one another: If there are 6 bad channels in one cluster/adjacent to one another, the participant will be excluded.Signal-to-noise ratio: As proposed by Parks, Gannon, Long, & Young [44], bootstrap resampling with a value of 9999 bootstraps of ERP waveforms will be used to calculate a signal-to-noise ratio confidence interval for each individual subject (a minimum of 25 trials). The lower bound of this calculation provides an objective measure of signal quality, and ensures that the components we are analyzing exceed a predetermined signal-to-noise ratio. Participants whose signal-to-noise ratio lower bound is below 3.0 dB will be excluded from the analysis. This specific value is within the accuracy peak of subject classification, and experienced ERP investigators have generally considered waveforms below 3.0 dB to be noisy when they are visually inspected.

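### Taken at face value, the sentence counts put both the active and the passive version of each frame in every participant's session, and neither the lists nor the analysis deal with repetition or voice order

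*Protocol article*

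**What the plan says.** The Abstract describes the experiment as "using 100 sentences (50 active and 50 passive sentences". The Materials section gives the same total: "Participants will read stimuli comprising 100 semantically reversible active and passive sentences". It adds that "there will be 200 filler trials consisting of questions" and cleft sentences.

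On list construction, Materials says: "There will be two lists of sentences each pseudorandomized into 10 sets (each set containing 10 experimental sentences and 20 fillers". The Procedure section describes a session of the same size, with "pauses after every block consisting of 30 trials (10 blocks in total".

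The sentences come in pairs. In Table 2 the active and the passive example share the first noun, the verb root, the adjunct, the second noun and the closing phrase. Materials says: "We will strive for active-passive pairing plausibility with the use of NP1 and NP2 that are plausibly reversible". The Frequency section speaks of verb pairs.

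The Statistical analysis plan section compares each participant's active and passive ERPs and switches the condition labels within participants. It has no term for presentation order or repetition. Under Predictions, the third outcome treats the absence of an effect at both the verb and NP2 as a sign that earlier findings were confounded by syntactic frequency.

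**The concern.** If 100 is the whole pool, made of 50 frames in two voices, a list of 100 holds both members of every pair. The two lists can then differ only in order. On meeting a frame for the second time, the participant has already read the same nouns, verb root, adjunct and closing phrase with the roles reversed.

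Two things could follow. If the voice effect is smaller on second reading, the averaged contrast shrinks. If one voice comes first more often, any general effect of repetition enters the contrast with a sign that depends on which voice leads. In fixed lists that imbalance is shared by everyone on the same list, so switching labels within participants does not remove it.

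Both bear on the main inference, because a null is to be interpreted and not just reported.

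**Working it through.** **1. Counts.** Per list: 10 sets x 10 = 100 experimental sentences and 10 x 20 = 200 fillers. Together that is 300 trials, which matches 10 blocks x 30 = 300. The article's session figures reproduce exactly.

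**2. Readings that fit or fail.**
- *Reading A:* 50 frames x 2 voices = 100 sentences. Each list of 100 is the whole pool, and each participant meets every frame twice.
- *Reading B:* 100 frames x 2 voices = 200 sentences, split by Latin square into two lists of 50 active + 50 passive. The counts per participant are the same and no frame is repeated.
- *A 50-frame Latin square* fails. It gives 50 sentences per list, not 100, and 25 per condition. The Data exclusion criteria say: "We determine a preset number of 25 trials per condition as a minimum". That minimum applies after artefact rejection, so one rejected epoch would exclude the participant.

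The article gives 100 as the total and nowhere mentions 200 experimental sentences, 100 frames or a Latin square. That favours A without proving it.

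**3. Table 3 as a check on the number of verb pairs.** 21513.1 x 50 = 1,075,655 and 26415.88 x 50 = 1,320,794. Both are whole numbers, as 50 pairs would require. But 40 to 42, 48 to 52, 100 and many other values also fit after rounding, so this does not decide between A and B.

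**4. What repetition does under Reading A.** Let D be the voice effect on first reading, a the proportion of it lost on second reading, R the main effect of repetition, and q the share of pairs read active-first. Then

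passive minus active = D[(1 - q) + q(1 - a)] + R(2q - 1).

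The article gives none of these values. With D = 1:
- Balanced order (q = 0.5): R cancels and the contrast is 1 - a/2. For a = 0, 0.25, 0.5 and 1 this is 1.00, 0.875, 0.75 and 0.50.
- Unbalanced order (q = 0.75, a = 0): the contrast is 1.5 for R = +1 and 0.5 for R = -1.

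**5. Illustration for power.** Single paired t-test, N = 50, two-sided 5%, noncentral t. The standardised effect dz = 0.404 is chosen because it gives 80% power; it does not come from the article. Order is balanced.

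| Loss on second reading (a) | dz | Power |
|---|---|---|
| 0 | 0.404 | 80% |
| 0.5 | 0.404 x 0.75 = 0.303 | 56% |
| 1 | 0.404 x 0.50 = 0.202 | 29% |

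**6. Illustration for type I error.** Suppose voice order were random in each of two independent lists. The SD of (2q - 1) is 2 x sqrt(50 x 0.25)/50 = 0.141 per list, and 0.141/sqrt(2) = 0.10 averaged over two. With SE = SD/sqrt(50), the error rate is 2 x P(Z > 1.96/sqrt(1 + (0.10R/SE)^2)).

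| Assumed R | Assumed SD 2 uV (SE 0.283) | Assumed SD 3 uV (SE 0.424) |
|---|---|---|
| 1 uV | 6.5% | 5.6% |
| 3 uV | 17.9% | 11.0% |

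These rates are averages over possible list orders. In the actual study the lists are fixed, and so is the bias.

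**The case against.** The strongest reply is that the article never says a participant reads both versions of a frame. Its statement that participants read 100 sentences can be taken as each reader's load, and counterbalancing is an ordinary reason for having two lists. Table 2 offers one example per condition and does not show how pair members are assigned. The sentences are in S1 Appendix, which is not shown, and the lists are pseudorandomised under constraints the article does not describe. This stands, and it is why the point is conditional.

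A reader might also infer that repetition necessarily pulls the contrast towards a null. The documents do not support that. A main effect of repetition cancels when voice order is balanced, and with unbalanced order the bias can go either way. Attenuation requires a smaller voice effect on second reading, for which the article gives no evidence.

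The figures in steps 5 and 6 are open to the same objection. Their inputs are assumed, a single t-test stands in for a cluster permutation test, and step 6 assumes no balancing at all, although the lists are pseudorandomised.

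Finally, the article provides two fillers per experimental sentence against habituation. That spaces the items out, but it neither keeps pair members apart nor balances which voice comes first.

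**Conclusion.** The point holds in conditional form. On the plain reading of the counts, each list contains both versions of every frame, and the analysis has no repetition or order term. That reading is likely, not certain.

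If it is right, the contrast averages first and second readings. With balanced order it keeps between 50% and 100% of the first-reading effect as the loss on second reading runs from complete to none. With unbalanced order it can be inflated or reduced. The power figures (80%, 56%, 29%) and the error rates (about 6% to 18%) illustrate possible size under assumed inputs; they are not properties shown by the article.

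The point deserves action, and not only a request for detail, because the third prediction draws a substantive conclusion from a null and the lists can be changed cheaply before data collection. If the design is in fact a 200-sentence Latin square, the concern falls away once the article says so.

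**What to change.** State the number of frames, what each list contains, and whether a participant reads one list.

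If both versions of a frame are in one list:
- Place the two members of each pair in opposite halves (sets 1-5 and sets 6-10). Each half has 5 x 10 = 50 experimental sentences, so use 25 actives and 25 passives per half.
- Make list 2 the mirror of list 1, so that each frame's voice order is swapped, and assign 25 participants to each list. The main effect of repetition then cancels in the contrast.
- Pre-specify a voice by presentation (first or second) test.
- Add a first-presentation-only sensitivity analysis. It has at most 25 trials per condition before artefact rejection, so it must be exempt from the 25-trial minimum.

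The cost is a re-sort of the lists before data collection and one or two additional tests. The first-presentation analysis uses half the trials and is less precise, so it should support the main analysis, not replace it.
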